## Abstract

**Background:**

People with mild intellectual disabilities (MID) are at elevated risk of substance-use problems. Beat the Kick is a motivation-focused, MID-adapted pre-treatment program. This trial aims to test whether Beat the Kick increases autonomous motivation to enter substance-use treatment versus care-as-usual (CAU), and to examine effects on substance use, satisfaction of basic psychological needs, treatment engagement, and acceptability.

**Methods:**

Open-label, multicenter superiority randomized controlled trial in the Netherlands. We will recruit 138 adults (≥ 18 years) with MID or borderline intellectual functioning (intelligence quotient (IQ) 50–85 with adaptive limitations) and hazardous substance use (Alcohol Use Disorders Identification Test (AUDIT) ≤ 19 or Drug Use Disorders Identification Test (DUDIT) ≤ 24; ≥ 12 months) from six intellectual-disability care organizations. Recruitment will be conducted jointly by researchers from Tilburg University and care professionals at the participating organizations. In a Zelen pre-randomization design, eligible clients will be randomized 1:1 to Beat the Kick or CAU using a centralized computer-generated sequence with variable block sizes, stratified by addiction type (alcohol vs cannabis/other drugs). Tilburg researchers will obtain informed consent after allocation (intervention: consent for intervention + assessments; CAU: consent for assessments only). As an open-label trial, only the statistical analyst will remain blinded to allocation via A/B-coded datasets; the allocation key is held by an independent coordinator until primary analyses are complete. Assessments occur at T1 (pre), T2 (post), T3 (1 month), and T4 (6 months). Safety is monitored at T2–T4 through systematic adverse event (AE) and serious adverse event (SAE) recording, and serious events are reported to the Ethics Review Board within 24 h.Primary outcome: autonomous motivation (Treatment Self-Regulation Questionnaire; 15 items; 1–5 scale). Secondary outcomes: substance use ( Substance Use and Misuse in Intellectual Disability Questionnaire (SumID-Q) with AUDIT (0–40; ≥ 8 hazardous; ≥ 20 probable dependence) and DUDIT (0–44; ≥ 6 men/ ≥ 2 women hazardous; ≥ 25 probable dependence)), satisfaction and frustration of psychological needs (Basic Psychological Need Satisfaction and Frustration Scale – Intellectual Disability Version (BPNSFS-ID); 24 items; 1–5), treatment engagement (yes/no), and participant satisfaction. Primary analyses will use intention-to-treat linear mixed-effects models with fixed effects for group, time, and group × time, adjusting for the stratification variable.

**Discussion:**

This study evaluates a motivation-focused, MID-adapted program under routine conditions. Anticipated challenges (open-label bias, retention) are addressed through exclusive trainer allocation per arm, supportive scheduling, and caregiver involvement. If effective, Beat the Kick could be integrated into standard practice to improve readiness for treatment, substance-use outcomes, and overall well-being in adults with MID.

**Trial registration:**

ISRCTN Registry, ISRCTN12571979. Registered on 11 June 2025. This trial was prospectively registered.

**Supplementary Information:**

The online version contains supplementary material available at 10.1186/s13063-025-09299-3.

## Administrative information

Note: the numbers in curly brackets in this protocol refer to SPIRIT checklist item numbers. The order of the items has been modified to group similar items (see http://www.equator-network.org/reporting-guidelines/spirit-2013-statement-defining-standard-protocol-items-for-clinical-trials/).

## Introduction

### Background and rationale {6a}

Substance abuse, defined as the harmful or hazardous use of psychoactive substances, including alcohol, tobacco, and cannabis, poses a significant challenge among people with mild intellectual disabilities (MID). In the Netherlands, a large study among 419 adults with MID/borderline intellectual functioning (BIF) receiving support from 16 disability services reported 64% current alcohol use, 62% smoking tobacco, and 15% cannabis or other illicit drug use (data collected 2010–2011) [1]. A 2019 systematic review (138 studies; 2000–2018) of international research on substance use and substance use disorders (SUD) in individuals with MID/BIF concluded that this group has elevated risks across diverse settings; for example, North American population-based data indicate SUD prevalences of roughly 6% in adults with intellectual disabilities versus ~4% in those without, while UK community cohorts reported about 1% diagnosed SUD in mixed-severity ID, with higher rates in clinical and forensic samples [2]. Consistent with this, a nationwide Swedish cohort using matched population and sibling comparisons found that individuals with MID had an increased risk of any substance use–related problem versus the general population (HR 1.82, 95% CI 1.73–1.91), which remained significant though attenuated in sibling analyses (HR 1.37, 95% CI 1.23–1.51) [3]. Together, these findings highlight both the national and international scope of the problem.

MID is characterized by limitations in intellectual functioning and adaptive behavior with onset during the developmental period; the mild range corresponds roughly to intelligence quotient (IQ) 50–55 to 70–75 [4]. In Dutch practice and service planning, individuals with borderline intellectual functioning (BIF; IQ 70–85) are often grouped with MID because they share many characteristics and face similar challenges in SUD care [5]. Reflecting this inclusive approach, this study first presents results for individuals with BIF; thereafter, “MID” is used to refer to both MID and BIF.

#### Barriers to treatment for individuals with MID

People with MID encounter significant barriers to addiction treatment, as services often fail to address their specific cognitive, emotional, and motivational needs. This contributes to health disparities, with unmet healthcare needs and limited access to effective interventions remaining common. For instance, mainstream addiction programs in the United States frequently exclude people with MID due to challenges in adapting to their needs [6]. In Canada, people with MID face considerable barriers in healthcare access, as general medical services often lack provider training, adapted communication strategies, and systematic support for their complex needs [7]. In Sweden, people with MID have been found to have an 81% higher risk of substance-related problems, particularly those with psychiatric comorbidities. Despite a well-developed healthcare system, inadequate tailored interventions and poor service coordination limit access to effective addiction treatment.

In the Netherlands, a significant treatment gap for people with MID and addiction was identified over a decade ago. A study using capture-recapture methodology showed that a substantial number of individuals with co-occurring MID and substance abuse disorders remained unidentified and unsupported by either care system [8]. Their findings highlighted how uncoordinated care between intellectual disability facilities and substance abuse treatment centers left many individuals undetected and unsupported by either system. Since then, several specialized treatment protocols and interdisciplinary teams have been developed to bridge this gap, including tailored screening tools, adapted cognitive-behavioral approaches, and initiatives aimed at improving collaboration between care providers. However, despite these advancements, such protocols have not been implemented consistently across services and regions. As a result, substantial disparities in access to coordinated and appropriate care remain, and the group previously shown to fall through the cracks of both systems continues to face exclusion risks [8].

Broader healthcare system issues exacerbate these challenges. Doherty et al. [9] identified several systemic barriers in primary care, including inadequate provider training, poor communication, and limited involvement of people with MID in decision-making. These barriers contribute to fragmented care and exclusion from essential services. Addressing these issues requires tailored addiction programs alongside systemic reforms, such as enhanced provider training, accessible communication strategies, and collaborative decision-making. Among the various barriers, low treatment motivation emerges as a particularly pivotal and modifiable factor. Research has shown that individuals with MID often experience limited insight into their substance use, struggle to articulate personal goals, and have difficulties initiating and sustaining treatment engagement [10, 11]. Motivation is a key predictor of treatment adherence and success across populations [12], and in the MID population it is closely linked to the quality of relational support and the extent to which autonomy, competence, and relatedness are supported [13]. However, most substance abuse services are not designed to foster these conditions.

As such, motivational barriers are not simply part of a broader problem—they are a core obstacle to effective care, and one that must be addressed first in order to enable access and engagement with treatment. This forms the rationale for the Beat the Kick intervention, which explicitly targets motivation as the primary outcome. Beat the Kick aims to strengthen autonomous motivation using approaches grounded in motivational interviewing and self-determination theory. By addressing this critical barrier, Beat the Kick seeks to create the conditions under which other forms of support can become accessible and effective.

#### Direct consequences of substance abuse

Substance abuse exacerbates vulnerabilities among people with MID, worsening mental and physical health and increasing social isolation. Cognitive limitations, such as difficulties in self-regulation and decision-making, can increase reliance on maladaptive coping (including substance use) [1]. These challenges compound common comorbidities such as anxiety and depression, creating barriers to effective care [2]. Evidence from a Swedish nationwide population-based cohort—linking national healthcare and population registers—shows that people with MID have a higher risk of any substance-use–related problem than the general population (HR 1.82, 95% CI 1.73–1.91), which remains elevated in sibling analyses (HR 1.37, 95% CI 1.23–1.51); risks are especially high with psychiatric comorbidity (e.g., bipolar disorder HR ≈ 8.22; psychotic disorder HR ≈ 6.52) [4]. In addition, studies in MID/BIF indicate that underlying motives (e.g., emotion regulation, social approval) are closely tied to the severity and frequency of use, underscoring the need for interventions that target these drivers [14].

#### Indirect consequences for caregivers and support networks

Substance abuse among people with MID also impacts caregivers and support networks, often leading to emotional exhaustion and strained relationships. Caregivers of individuals with MID and comorbid psychiatric disorders have been shown to experience significantly higher levels of stress and psychological distress, largely due to the complexity of the care required [15]. This underscores the importance of providing caregivers with specialized support and training. When substance abuse becomes more severe, caregivers and support networks often face additional burdens, as they must manage escalating behavioral and emotional challenges. This highlights the need for targeted, personalized interventions that not only address substance abuse itself but also support the broader network surrounding the individual.

#### Current therapeutic approaches

Evidence-based approaches such as cognitive behavior therapy (CBT) have demonstrated efficacy in addressing substance use disorders in people with MID when appropriately adapted [16]. Key adaptations include simplified language, visual aids, and concrete examples to enhance accessibility [17]. Motivational Interviewing (MI), which emphasizes intrinsic motivation through a person-centered approach, has also proven effective in fostering autonomy and sustainable behavioral change [18]. Research has shown that MI is applicable to individuals with MID, provided that techniques are tailored to their language level, cognitive abilities, and tendency toward socially desirable responses [13]. Additionally, certain professional characteristics—such as trustworthiness, engagement, and empathy—are essential for optimizing treatment motivation and outcomes.

CBT interventions have shown promise in improving mental health outcomes for people with MID, though more robust, long-term trials are needed to confirm these findings [19]. While much of the existing research focuses on group-based CBT formats, it is also relevant to examine whether CBT-based approaches that incorporate motivational interviewing, such as Beat the Kick, are effective in the Dutch context. This combination targets emotional regulation and self-awareness while enhancing treatment engagement and outcomes [20, 21].

#### Development and evidence supporting Beat the Kick

The Dutch Beat the Kick intervention is a specialized pre-treatment program designed to meet the cognitive, emotional, and motivational needs of individuals with intellectual disabilities (Table 1). It integrates CBT and MI to build foundational skills and enhance motivation, addressing key barriers to treatment engagement and effectiveness (22, 23). Adapted CBT approaches are particularly effective in managing co-occurring conditions like anxiety, which often exacerbate substance use issues [22].

**Table 1 Tab1:** Beat the Kick intervention

Beat the Kick intervention	Time (minutes)	Attendees
Recommendation:		
Intake with administration of SumID-Q	60 min	
Beat the Kick sessions	45–60 min	Trainer and participant
• 1: The first acquaintance		
• 2: Focusing on the participant’s use		
• 3: When are you addicted?		
• 4: When do you get urges?		
• 5: Urges: How do they work?		
• 6: The 3Cs: Catching, checking and changing		
• 7: What to do when you get the urge?		
• 8: Genogram		
• 9: Take Care card		
• 10: Closing session		

An initial evaluation using a single-case experimental design (SCED) demonstrated the promise of Beat the Kick in improving outcomes for people with intellectual disabilities [21]. However, while SCEDs offer strong internal validity, they are limited in generalizability, necessitating complementary randomized controlled trials (RCTs) to test efficacy in more representative samples (Bhatt and Gentile, 2021).

#### Global potential and future research

Beat the Kick addresses a critical gap in addiction treatment for people with MID. While countries such as Canada, the UK, and the USA recognize the need for similar interventions, progress is hindered by a lack of evidence-based models [6]. Large-scale RCTs could rigorously test the program’s efficacy and establish it as a structured, evidence-based pre-treatment approach within addiction care.

#### Proposed effectiveness study

A randomized controlled trial will evaluate the effectiveness of Beat the Kick in enhancing motivation for treatment, improving substance use outcomes, and increasing mental health and treatment engagement compared to standard addiction treatments. Insights from this study will inform best practices for addiction treatment and contribute to reducing health disparities for people with MID globally.

### Objectives {7}

#### Primary objective

The primary objective of this RCT is to evaluate the effectiveness of the Beat the Kick intervention compared to care-as-usual (CAU) in adults with MID, focusing on enhancing autonomous motivation for substance abuse treatment. The central hypothesis is that individuals receiving the Beat the Kick intervention will show greater improvement in autonomous motivation for engaging in substance abuse treatment from pre-test to post-test compared to those in the CAU group.

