### Eligibility criteria {10}

#### Inclusion criteria

Participants are eligible if they meet the following criteria:MID or BIF: Defined by an IQ of 50–70 (MID) or 70–85 (BIF) combined with severe adaptive functioning limitations (defined by significant impairments in at least two of the following domains: conceptual, social, and practical skills, as outlined in the DSM-5). Both groups are collectively referred to as “individuals with MID,” reflecting their shared characteristics and support needs. In the Netherlands, these groups qualify for specialized mental health care and are often grouped in research, practice, and policy contexts [5].Substance abuse: Hazardous alcohol or drug use that negatively impacts physical, psychological, interpersonal, or social well-being for a duration of at least 12 months [10]. To focus the intervention on individuals with problematic substance abuse rather than severe substance use disorders, participants with indications of high-intensity or clinically complex use patterns will be excluded. This will be assessed using the Substance Use and Misuse in Intellectual Disability Questionnaire [24], which includes the Alcohol Use Disorders Identification Test (AUDIT) and the Drug Use Disorders Identification Test (DUDIT) to screen for substance abuse severity. Participants who exceed the established clinical thresholds for high-risk use (AUDIT > 19 or DUDIT > 24) will not be eligible to participate, as their level of use suggests the need for more intensive, specialized addiction care [24, 25].Lack of autonomous motivation: Participants must exhibit low autonomous motivation to change their substance use, as this is the primary target of the intervention. Autonomous motivation will be measured using the Treatment Self-Regulation Questionnaire (TSRQ) [21], which assesses the extent to which individuals engage in change based on personal value, interest, or internal goals [26]. This criterion ensures that the intervention is tested in individuals who are not yet ready or internally motivated to change, in line with the study’s aims.Age: Participants must be 18 years or older to ensure legal competence for informed consent and appropriateness of intervention content.Language proficiency: Participants must have sufficient Dutch language proficiency (minimum B1 level) to understand the intervention content, complete study measures, and engage in therapeutic conversations. This ensures the validity of assessments and meaningful participation.

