### Outcomes {12}

The primary outcome is the change in autonomous motivation for substance-abuse treatment, measured using an adapted version of the TSRQ [21]. The TSRQ comprises 15 items rated on a 5-point Likert scale (1 = completely untrue; 5 = completely true). Subscales are scored as means (range 1–5) and include autonomous motivation (internal consistency α≈0.84; primary endpoint), controlled motivation (α≈0.78), and amotivation (α≈0.41; analyzed exploratorily due to lower reliability). As participation in the intervention and any subsequent treatment is voluntary, baseline motivation may be relatively high; this will be considered when interpreting change. Assessments will occur at pre-treatment (T1), post-treatment (T2), and follow-ups at 1 month (T3) and 6 months (T4), with the primary endpoint defined as Δ(T2–T1) on autonomous motivation and maintenance examined at T3/T4. To optimize comprehension for MID/BIF participants, all self-reports will be interviewer-assisted.

Secondary outcomes include reductions in substance use and related problems, measured with the SumID-Q (patterns, frequency, consequences), which embeds the AUDIT and DUDIT screens. The AUDIT has 10 items (item scores 0–4; total 0–40) with commonly used cut-offs ≥ 8 for hazardous use and ≥ 20 for probable dependence. The DUDIT has 11 items (item scores 0–4; total 0–44) with cut-offs for hazardous use of ≥ 6 for men and ≥ 2 for women, and ≥ 25 for probable dependence. Both continuous totals and categorical classifications (none/hazardous/probable dependence) will be analyzed at T1, T2, T3, and T4 (recall periods per instrument guidance). Psychological need satisfaction and frustration will be assessed with the Basic Psychological Needs Satisfaction and Frustration Scale – Intellectual Disabilities (BPNSFS-ID; 24 items, 5-point Likert), yielding mean scores (range 1–5) for autonomy, competence, and relatedness (higher satisfaction = greater fulfillment; higher frustration = greater need thwarting) at T1, T2, T3, and T4 [35].

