## Measures

### Plans for assessment and collection of outcomes {18a}

The primary outcome of this study, autonomous motivation, will be assessed using an adapted version of the TSRQ specifically tailored for substance abuse [21]. The TSRQ comprises 15 items divided into four subscales: autonomous motivation (e.g., “I would change my use because I choose to”), controlled motivation (e.g., “I would change my use because others expect me to”), and amotivation (e.g., “I am not at all concerned about why I would change my use”). Participants will respond on a 5-point scale from “completely untrue” to “completely true.” Mean scores for each subscale will be calculated by summing the corresponding items and dividing by the number of items. Previous studies have demonstrated strong reliability for the TSRQ, with Cronbach’s alpha values exceeding 0.73 for most subscales; however, amotivation has a lower reliability (α = 0.41). Autonomous motivation is associated with positive health outcomes, whereas controlled motivation correlates with negative outcomes [26].

Psychological need satisfaction and frustration will be measured using the BPNSFS-ID [35], adapted from the original BPNSFS [38]. This scale evaluates satisfaction and frustration across three psychological needs: autonomy, relatedness, and competence, comprising 24 items (eight items per need). Responses are rated on a 5-point Likert scale from 1 (“completely untrue”) to 5 (“completely true”). The BPNSFS-ID demonstrates high internal consistency (overall Cronbach’s alpha = 0.92) and robust factorial structure, with subscale alphas ranging from 0.78 to 0.92 and test-retest reliability ranging from 0.68 to 0.83 over two weeks. This study aims to explore whether the intervention influences substance use by impacting the satisfaction or frustration of these needs, potentially elucidating mechanisms underlying the intervention’s effectiveness.

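### The primary objective names motivation for treatment, but the entry criterion and every TSRQ item shown concern motivation to change one's own use

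*Protocol article*

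**What the plan says.** Four places make treatment the object of the motivation:

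- Abstract, Background: the trial tests whether the programme "increases autonomous motivation to enter substance-use treatment versus care-as-usual (CAU").
- Objectives {7}, Primary objective: the hypothesis is "greater improvement in autonomous motivation for engaging in substance abuse treatment from pre-test to post-test compared to those in the CAU group".
- Outcomes {12}: "The primary outcome is the change in autonomous motivation for substance-abuse treatment, measured using an adapted version of the TSRQ".
- Statistical methods {20a}: the primary objective is repeated, again as motivation for treatment.

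Two places make the person's own substance use the object:

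- Inclusion criteria: "Participants must exhibit low autonomous motivation to change their substance use, as this is the primary target of the intervention". The same paragraph says that this is measured with the TSRQ.
- Plans for assessment {18a}: the scale is said to be tailored to substance abuse, and one example item is given for each subscale named. For the endpoint subscale it is "autonomous motivation (e.g., “I would change my use because I choose to"; for the controlled subscale, "controlled motivation (e.g., “I would change my use because others expect me to". The amotivation example also refers to changing use.

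The operational endpoint is clear: the autonomous subscale mean (range 1–5), "with the primary endpoint defined as Δ(T2–T1) on autonomous motivation and maintenance examined at T3/T4".

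**The concern.** Wanting to change one's use and wanting to enter treatment are different things. A participant who decides to cut down alone, for reasons of their own, could score as a success on items like the one shown and still want no treatment.

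The programme makes that route plausible. Intervention description {11a} says that it aims to help participants alter their patterns of use, with sessions on triggers, responses to craving and substitute activities. The Exclusion criteria also remove anyone already planning other substance-use treatment, so participants start without a plan to enter it.

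At stake is what the primary result can be said to show. Followed as written, a significant difference between arms in the T1 to T2 change would be reported as greater autonomous motivation for treatment. For a pre-treatment programme that is the central claim, and the Abstract's Discussion links success to readiness for treatment. The items as described ask about something else.

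**Working it through.** The check is a comparison of text; no arithmetic decides it.

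**Step 1. What is the motivation for, and what does each place do with it?**

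| Place | Object of the motivation | Use |
|---|---|---|
| Abstract, Background | Entering treatment | Trial aim |
| Primary objective | Engaging in treatment | Objective and hypothesis |
| Outcomes {12} | Treatment | Label of primary outcome |
| Statistical methods {20a} | Treatment | Objective behind the model |
| Inclusion criteria | Changing use | TSRQ entry criterion, called the primary target |
| {18a}, autonomous item | Changing use | Example from the endpoint subscale |
| {18a}, controlled item | Changing use | Example, other subscale |
| {18a}, amotivation item | Changing use | Example, other subscale |
| Abstract, Methods | None stated | Primary outcome named without an object |

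The treatment wording recurs in four places, so it is not a slip. Among the example items, 3 of 3 refer to changing use and none to treatment. The scale has 15 items, so 15 − 3 = 12 are not shown.

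**Step 2. Does the protocol treat the two as the same?** It does not say so. The Discussion lists raising motivation for change and stimulating treatment engagement as two things to be evaluated. Sections {11b} and {11d} take voluntary treatment entry as a sign of greater motivation to change. That inference runs from entry to motivation to change. The reported conclusion would need the other direction: from a higher score on changing use to motivation for treatment.

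**Step 3. What else measures treatment?** Outcomes {12} records start of formal treatment (yes/no) within the T3 window and, separately, follow-through on referrals (yes/no). Section {18a} says that engagement will be verified through the care provider or treatment records and will serve as a behavioural indicator of motivation to engage with care. Sections {11b} and {11d} also provide for recording voluntary treatment entry during the study. All of these measure uptake, and none is the primary endpoint.

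**Step 4. Does this touch the sample size?** No. The stated figures reproduce with the between-groups repeated-measures F test, using the inputs in Sample size {14}: f = 0.25, m = 4 measurements, ρ = 0.5, two groups, α = 0.05.

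- λ = f²·N·m / (1 + (m − 1)ρ) = 0.0625 × 82 × 4 / 2.5 = 8.2, with 1 and 80 degrees of freedom. Power is 0.808, so N = 82 as stated.
- 82 / (1 − 0.40) = 136.7, hence 137, or 138 for equal arms, as stated.

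These inputs do not depend on what the motivation is for, so relabelling the endpoint leaves both figures as they are.

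**The case against.** The strongest reply is that this is unharmonised wording around an endpoint that is operationally clear. Instrument, subscale, time points and test are fixed, and the preferred remedy changes none of them. The three items are offered only as examples, one of them from the endpoint subscale, and an article need not print the whole scale. The protocol also has a coherent logic: its Background presents motivation as the obstacle to be tackled first so that treatment becomes accessible, and treatment uptake is measured as well. A TSRQ gain without uptake would therefore be visible.

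Much of this stands, and it limits the point. A reader might infer that a positive result could not support the stated conclusion at all. The documents do not show that: treatment-worded items among the 12 unseen ones cannot be excluded, the two motivations may be related, and uptake is recorded. A reader might also infer that the yes/no engagement outcome is the only treatment-specific measure. That is not so, because follow-through on referrals is recorded too.

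What the reply does not remove is the disagreement itself. The objective, hypothesis and outcome label name one construct, while the entry criterion and all the items shown name another. The uptake outcomes help interpretation, but they do not turn a score on changing use into a measure of motivation for treatment.

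**Conclusion.** The point holds in limited form. The protocol gives its primary endpoint two different constructs, and on the instrument as described a gain from T1 to T2 would not by itself directly support a conclusion about motivation for treatment. It would support a conclusion about motivation to change use.

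The effect falls on the interpretation of the primary result, not on its estimate, test or sample size. How far the two constructs diverge in this population cannot be computed from the document.

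The conclusion assumes that the example items are typical of the autonomous subscale. Because 12 of 15 items are unseen, confidence is moderate. The matter should be corrected, since it decides what the trial may claim and costs little. It is not something an analysis plan could settle, because no analysis changes what the items ask.

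**What to change.** Make every section name one construct.

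- **Preferred:** restate the primary objective, hypothesis and endpoint label as autonomous motivation to change substance use. This affects the Abstract (Background), the Primary objective, Outcomes {12} and Statistical methods {20a}, plus the registry entry where it carries the same wording. The text then agrees with the Inclusion criteria and {18a}. Rest any claim about entering treatment on the engagement and referral outcomes. The Abstract's Methods paragraph makes no treatment claim for the primary outcome and needs no correction.
- **Alternative:** if the full adapted scale does refer to treatment, show this, and correct the Inclusion criteria and the examples in {18a} to match.

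Rewording the item stem to ask about treatment is not advised. The same TSRQ serves as the entry measure, so eligibility would change too. The cited reliability (α≈0.84 for the autonomous subscale) might not carry over to new wording. Trial status also expected recruitment to start in July 2025.

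The cost of the preferred change is edits to the text and possibly a registry update. The downside is a narrower headline claim.
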